### SMILE Tools: Overview

The intervention is delivered through 2 components: the SMILE Game App and the SMILE Companion App. Participants download and use both apps, which are required for participation. Both apps use the same login credentials and are linked through a single account. Both the Game and Companion apps are designed for use across age groups and in a manner that supports simultaneous accessibility for both adolescents and young adults; it was not feasible within the study constraints to provide age-specific content as originally planned.

### SMILE Game App

The game follows a player who moves to the cyberpunk city of Hopetown with their sister, Seraphina. In this world, automatic thoughts appear as small, robot-like creatures. When a cybernetic dragon attacks the city and captures Seraphina, the player embarks on a quest to rescue her. Guided by key characters, the player learns CBT-based techniques to understand and manage negative automatic thoughts. Across 5 story-driven modules, players engage in interactive challenges designed to promote cognitive restructuring, resilience, and healthier thinking patterns.

Module 1: “Hopetown.” The player investigates the city’s attack and discovers that the villain manipulates citizens’ negative automatic thoughts. Challenges introduce the CBT “hot cross bun” model [48], teaching players to distinguish between thoughts, feelings, bodily sensations, and behaviors, identify automatic thoughts, and recognize cognitive distortions.

Module 2: “Starfall District.” In a corrupted district, the player helps NPCs trapped in negative thinking cycles. This module deepens understanding of the links between thoughts, feelings, bodily sensations, and behaviors and introduces cognitive restructuring and paced breathing as tools for breaking negative cycles and strengthening emotional regulation and resilience.

Module 3: “The Technicians’ Quarters.” The player uncovers the technician’s core beliefs to unlock key information to find their sister. This module focuses on identifying and challenging core beliefs. During a fight-or-flight scenario, players must actively apply previously learned CBT-based tools to overcome negative automatic thoughts.

Module 4: “Library.” While searching for information to defeat the villain, the player evaluates evidence and tests the validity of competing narratives. This module strengthens critical thinking and evaluation skills, reinforcing cognitive restructuring and self-regulation techniques.

Module 5: “The Data Vault.” In the final confrontation, the player applies all acquired skills to defeat the villain and rescue Seraphina. A closing social scenario requires assertive communication, targeting fear of negative evaluation, reducing avoidance, and strengthening social confidence through behavioral practice.

### SMILE Variants: Feedback vs No-Feedback

Clusters of participants are randomized (see details in the “Randomization: Proof-of-Concept Study” section below) to either a feedback or a no-feedback variant of SMILE. The feedback component is expected to function as an intrinsic motivator for engagement and learning and to facilitate greater transfer of skills acquired in the game to real-world experiences. The feedback system is based on Nicholson’s [49] “Recipe for Meaningful Game Engagement” and delivered via the SMILE Companion App. Feedback is generated across time points using a triad of data sources: in-game metrics, ESMs, and self-report measures. Upon completion of each module, players receive feedback and are invited to explore specific time points of interest. The system provides brief, automated summaries (eg, “your mood appeared to be slightly more positive than earlier in the day”), linking contextual and gameplay data with daily mood and well-being ratings. The SMILE Companion App (see below for more details) presents this feedback in graphical form, integrating in-game, ESM, and reflective exercise data. Visualizations include simple daily averages, trends over time, and basic associations between activity, context, and well-being. Players can select specific indicators to explore how they relate to in-game activities, real-world experiences, and other measured variables. Participants assigned to the no-feedback condition complete the same game modules, ESM prompts, and reflective exercises, but do not have access to personalized feedback or data visualizations.

### SMILE Companion App

The SMILE Companion App supports self-monitoring, feedback, and data collection during the proof-of-concept trial. All participants are required to use the app, as baseline and first-week outcome assessments are mandatory. The app delivers self-report measures, ESM prompts, and diary entries via push notifications. Participants can individually adjust the timing of these prompts to fit their daily routines. In addition, users can customize selected features (eg, light or dark mode) and receive rewards for completing study activities. The app also provides an overview of study progress, including the current module, scheduled play periods, and pending questionnaires.

Participants assigned to the feedback condition receive personalized feedback within the app. The feedback acts as an intrinsic motivator for engagement and a link between the skills learned in the game and real-world scenarios and experiences. This feedback is delivered to only half of the sample to evaluate its effectiveness. Feedback is based on Kolb’s experiential learning model [50], Gibbs’ Reflective Cycle [51], and Nicolson’s recipe [49] for linking experiential learning from the game, feelings from the ESM measures, analysis, presented in graphical form from the in-game measures and decision-making in the cognitive restructuring exercises. Reflections on these elements are then used for real-life goal-planning strategies. The clusters of participants who do not receive the feedback will still participate in the game and ESM exercises, but will not be able to visualize and reflect on their data.

### Study Design

#### Proof-of-Concept Study

The protocol follows the SPIRIT (Standard Protocol Items: Recommendations for Interventional Trials) guidelines [52], with the checklist available in Checklist 1.

This proof-of-concept study uses a cluster-randomized, multisite, multiarm adaptive trial design. Participants are grouped into clusters (see Participants Recruitment and Procedure), which are allocated to 1 of 3 sequences based on feasibility. Each cluster is subsequently randomized to either feedback or a no-feedback variant of the intervention. Clusters assigned to Sequence 1 complete a neutral baseline period with ESM, followed by Game Modules 1‐2. Clusters in Sequence 2 complete the baseline period and Game Modules 1‐4. Clusters assigned to Sequence 3 complete the baseline period and all 5 game modules (Figure 1).

The adaptive trial design is based on an initial site-level sample size calculated under the assumption that all steps in the sequence will be completed. Two stages of adaptive interim analyses will be conducted to estimate the effects of each intervention modality, including the control condition. Based on these interim results, sample sizes per cluster or site may be adjusted and decisions may be made to amend or discontinue specific intervention elements. Each adaptive interim analysis will estimate effects on the primary outcomes and identify key predictors of these effects. Sample sizes and randomization sequences may be updated accordingly. Additionally, active intervention elements may be modified based on model parameters, including patterns of feature use and the contribution of intervention-related indicators to interim effect sizes. The trial will be complemented by a process evaluation [53], using a mixed-methods realist evaluation approach. This design enables the assessment of multiple aspects of the proof-of-concept study (ie, acceptability, feasibility, reach, and efficacy). In particular, it supports the estimation of efficacy with a low risk of bias (eg, by minimizing contamination between experimental and control periods), while also allowing for in-depth process evaluation and enhancing the generalizability of findings in a naturalistic field setting.

The intervention is rolled out over a 10-month period from September 2025 to June 2026. Three sequences are planned, separated by 3-week intervals; however, the length of the interval may vary depending on any implemented modifications. Clusters are allocated to sequences based on site-specific feasibility and readiness, meaning that clusters enter the rollout at different points depending on when they are prepared to initiate the intervention. Consequently, the number of clusters varies across sequences. In total, 46 clusters across 7 pilot sites will be included in the rollout. Each game module is designed to last no longer than 20 minutes. With 5 modules in total, including all study measures, participants are expected to spend a maximum of approximately 4.5 hours on the study, distributed over several weeks.

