Hypothesis 1 (primary): compared with the control period, anxiety and depression scores (primary outcomes) will be lower in the experimental conditions (ie, with and without feedback) at posttest.Hypothesis 2 (secondary): compared with the control period, the secondary outcomes (well-being, resilience, emotion regulation, and self-efficacy) will be higher and social anxiety lower in the experimental conditions (ie, with and without feedback) posttest.Hypothesis 3 (secondary): feedback obtained in one of the experimental conditions will be positively associated with the feasibility, acceptability, and preliminary efficacy of the SMILE tools.

Our second aim is to identify contexts, psychological processes, and mechanisms of change, and how these are associated with outcomes of the intervention in participants. To this end, we will test the following hypotheses:

Hypothesis 4 (secondary): compared with the control period and the experimental condition without feedback, well-being and resilience will be higher in the experimental condition with feedback posttest.Hypothesis 5 (tertiary): multimodal digital observable cues (language, speech, and facial markers), collected using diary recordings, will discriminate between children, adolescents, and young adults under mental distress and those without. Moreover, the digital observable cues will discriminate between anxiety and depression and severity.

Finally, we will conduct exploratory analysis to map digital biomarkers from in-game metrics and diaries to subjective anxiety and mood scores collated from in-game, ESM, and reflective exercises from the SMILE Companion App.

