### Measures in the Proof-of-Concept Study

There are 7 types of data that we will collect in this phase. First, there are self-reported primary and secondary measures that will be collected at the following time points (Table 2): baseline (T0; 1 to 2 weeks before the intervention), right before the intervention (T1), during the intervention (T2), and at posttest (T3; after completion of the intervention). Additionally, measures of depression and anxiety (ie, primary outcomes) will be distributed on a weekly basis, alternating between a depression scale 1 week and an anxiety scale the next. Secondary measures (ie, well-being and resilience) will be collected every other week. Second, participants will be invited to respond to a short daily survey using ESM, 5 times a day (Table 3). Third, there will be in-game measures related to the current activity in the game (Table 1). Fourth, we will collect vocal and facial data via weekly diary recordings. Fifth, we will assess the feasibility and acceptability of the game through measures other than participants’ responses. Finally, we will collect user data that are restricted to the SMILE apps: the Game App and the Companion App. All measurements described below will be collected by the SMILE end user apps.

**Table 2. T2:** Study measures and time points.

Variable	T0^a^	T1^b^	T2^c^				T3^d^
	Sequence 1			Sequence 2		Sequence 3	Posttest
	Week 1	Week 2	Week 3	Week 4	Week 5	Week 6	
Anxiety	✓	✓		**✓**		**✓**	**✓**
Depression	✓	✓	**✓**		**✓**		**✓**
Well-being	✓	✓		**✓**		**✓**	**✓**
Resilience	✓	✓		**✓**		**✓**	**✓**
Privacy concerns	✓						
Acceptance (of SMILE^e^ Game App)							**✓**
Acceptance (of SMILE Companion App)							**✓**
User experience (in SMILE Game App)							**✓**
User experience (in SMILE Companion App)							**✓**

a T0=Time 0 (before baseline period).

b T1=Time 1 (before the start of the game).

c T2=Time 2 (during the game period).

d T3=Time 3 (after the intervention).

e SMILE: Supporting Mental Health in Young People: Integrated Methodology for Clinical Decisions and Evidence-Based Interventions.

**Table 3. T3:** Data collected via experience sampling methods.

Variable	Morning	Midday	Midday	Midday	Evening
Sleep quality	✓				
Mood		✓	✓	✓	✓
Location		✓	✓	✓	✓
Activity context		✓	✓	✓	✓
Social context		✓	✓	✓	✓
Stress coping		✓	✓	✓	
Emotion regulation		✓	✓	✓	✓
Reflective functioning					✓
Social anxiety^a^		✓	✓	✓	
Self-efficacy^a^					✓

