### Data Analysis Plan

#### Proof-of-Concept Study

Hypotheses regarding the preliminary efficacy of the SMILE interventions will be examined using linear mixed-effects models (LMMs), fitted separately for each primary and secondary outcome. For outcomes assessed using age-specific scales, raw scores will be transformed to z scores or percentages to facilitate comparability across age groups. Models evaluating linear time-on-treatment effects will include fixed effects of time (calendar time and exposure time), condition (game with feedback, game without feedback, and baseline control), and the exposure time by condition interaction. We will also consider models including age and gender as covariates, with the final specification determined on the basis of model comparison. The random-effects structure will reflect the hierarchical design, with 3 levels: country, cluster, and individual. To account for outcome variability over calendar time, we will additionally include random effects for the cluster by calendar time and individual by calendar time components. Analyses will be conducted on the minimum-dose intention-to-treat sample, defined as participants who complete baseline assessments and at least one game module. Given the exploratory nature of this pilot, *P* values will be interpreted descriptively.

Adaptive interim analyses will be performed at the end of each sequence to estimate the empirical effects on primary and secondary outcomes. Predefined criteria for adjustment include potential changes to the primary outcomes, sample size, and intervention elements. First, if limited variance is observed in the primary outcomes of depression and anxiety, for example, if more than 80% to 90% of participants score within the top or bottom 10% of the scale, we will consider promoting well-being outcomes to the primary outcomes. This change would be accompanied by a recalculation of the required sample size based on the expected effect size for the revised primary outcome. Second, interim results may be used to adjust the planned sample size, including the number and/or size of clusters. Third, we will consider adaptations to intervention elements based on interim findings on engagement and the delivery of feedback, including changes to game modules or modes of interaction and adjustments to the level or detail of feedback provided in subsequent intervention sequences.

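### The primary game-versus-control contrast is an uncontrolled before-after comparison, so the claim of low risk of bias does not hold for it

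*Protocol article*

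**What the plan says.** All references are to the protocol article.

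- **Primary hypothesis** (Proof-of-Concept Study, Hypothesis 1): "compared with the control period, anxiety and depression scores (primary outcomes) will be lower in the experimental conditions (ie, with and without feedback) at posttest".
- **What the control is** (Study Design): "Clusters assigned to Sequence 1 complete a neutral baseline period with ESM, followed by Game Modules 1‐2". Sequences 2 and 3 follow the same order with more modules. The Data Analysis Plan codes "condition (game with feedback, game without feedback, and baseline control" as the levels of one factor.
- **When it is measured** (Measures): "baseline (T0; 1 to 2 weeks before the intervention), right before the intervention (T1), during the intervention (T2), and at posttest (T3". Both control measurements precede the game in every participant.
- **What is randomised** (Randomization): only the feedback or no-feedback variant, by cluster. Under SMILE Variants, both variants receive the same modules.
- **Entry to sequences** (Study Design): "Clusters are allocated to sequences based on site-specific feasibility and readiness".
- **Calendar**: "Three sequences are planned, separated by 3-week intervals", with intervals that may vary. The Data Analysis Plan places an interim analysis at the end of each sequence. The Results section says two sequences were complete before the third began, with clusters joining the third on a rolling basis.
- **The claim** (Study Design): "it supports the estimation of efficacy with a low risk of bias (eg, by minimizing contamination between experimental and control periods".
- **Limitations** (Discussion): sample representativeness, participant feedback that cannot be acted on in time, dropout in an unguided intervention, device access and self-report. The before-after nature of the primary contrast is not among them.

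**The concern.** Limited contamination between periods is the only reason offered for low risk of bias. Contamination is not the main threat to a contrast in which every participant moves from baseline to game in that order. Three other influences coincide with the switch: repeated questionnaires (T0, T1, then weekly), the school year over a September-to-June rollout, and natural change in mood. A randomised concurrent no-game group would separate these from the game, and the trial has none.

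The article says its findings will inform the design of a definitive randomised trial. If anxiety or depression falls between baseline and posttest, the text as it stands invites readers to credit the game with that fall on the strength of a property the design lacks.

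**Working it through.** **1. Which contrast has which protection**

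- Game versus control period (Hypothesis 1): same clusters, fixed order, not randomised, no concurrent comparator by design.
- Feedback versus no feedback (part of Hypotheses 3 and 4): randomised by cluster and concurrent, but both arms play the game.

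The low-risk-of-bias sentence speaks of experimental and control periods, so it refers to the first contrast. The randomisation protects only the second.

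**2. What calendar-time adjustment can do**

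The Data Analysis Plan includes calendar time and exposure time as fixed effects but does not fix their form. Take two baseline weeks followed by game weeks, giving 4, 6 and 7 weekly observations in Sequences 1, 2 and 3. The start weeks below are assumptions.

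- *Sequences do not overlap, calendar week as a factor.* There are 4 + 6 + 7 = 17 distinct weeks. In each week all active clusters are in control or all are in game, so the game column is a sum of week columns. The design matrix has rank 17 for 18 columns (intercept, game, 16 week indicators), and the game effect is not estimable.
- *Starts three weeks apart (weeks 0, 3, 6).* Rank is 14 of 14; estimable.
- *One-week stagger within each sequence.* Rank is 21 of 21; estimable.
- *No overlap, linear calendar time.* Estimable, with standard error about 0.035 SD (41 per cluster, 4 clusters per sequence, ICC 0.01, autocorrelation 0.60). A 0.10 SD retest drop after T0, with no true effect, still biases the game effect by about -0.04 SD.

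Estimability therefore comes either from an assumed shape of time or from overlap produced by readiness-based entry. Neither gives the protection of randomisation.

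**3. Illustration of the consequence**

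The concern disputes no figure in the plan. The Sample section's 992 is used only to obtain completers. It already includes the 50% dropout, so 992 × 0.5 = 496.

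Inputs: N = 496; within-participant autocorrelation 0.60 (Sample section); α = 0.05, taken as two-sided because sidedness is not stated; true effect zero. The shift δ is assumed.

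SE of a mean pre-post change in SD units = √(2(1 − 0.60)/496) = √(0.80/496) = 0.0402.

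Probability of a significant result = Φ(δ/SE − 1.96) + Φ(−δ/SE − 1.96).

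| Non-game shift δ (SD) | δ/SE | Declared significant |
|---|---|---|
| 0 | 0 | 5% |
| 0.02 | 0.50 | 8% |
| 0.05 | 1.25 | 24% |
| 0.10 | 2.49 | 70% |
| 0.20 | 4.98 | >99% |

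Cluster-level variation over time changes little. With ICC 0.01, an assumed cluster autocorrelation of 0.8 and 46 clusters, the added variance is 2 × 0.01 × 0.2/46 = 0.00009. The SE becomes √(0.00161 + 0.00009) = 0.0412, and the rates at 0.05 and 0.10 SD are about 23% and 68%.

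**The case against.** The strongest reply is that this is a proof-of-concept study. The article speaks of preliminary efficacy, calls itself exploratory, interprets P values descriptively and defers the definitive answer to a later trial. A before-after contrast with two pre-game measurements is a recognisable choice for that purpose, and the hypothesis openly names a control period. All of this stands, and the design choice itself is not the fault. It does not make the low-risk-of-bias sentence true, and the limitations do not warn the reader.

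A reader might infer more than the documents support:

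- *That the game effect cannot be estimated at all.* This is so only if cluster calendars do not overlap and calendar week is a factor. The interim analysis at the end of each sequence and the Results section point to successive sequences. However, the article also says clusters enter at different points as they become ready, participants play at their own pace, the form of calendar time is left open, and Figure 1 is not shown.
- *That the bias has a known size.* With starts at weeks 0, 10 and 24, linear calendar time and an assumed drift of -0.03 SD per week, the apparent effect is -0.07 SD at 2 weeks and -0.16 SD at 5 weeks. With sequence intercepts and a constant game effect, the same drift gives zero bias. The drift is assumed, so these figures are scenarios.
- *That the randomised contrast can carry the efficacy claim instead.* Both arms play the same game, so it cannot show whether the game lowers anxiety or depression. Its power of about 0.83-0.85 assumes that feedback alone adds 0.20 SD, with 46 equal clusters, 496 analysable participants and cluster autocorrelation of 0.8 to 1. At 0.10 SD it is about 0.31-0.32.

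**Conclusion.** The low-risk-of-bias statement is wrong as written for the primary contrast. That follows from the text alone: own earlier baseline as control, fixed order, randomisation of feedback only, and readiness-based entry. It needs no assumption about drift.

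The size of any bias is unknown. The 24% and 70% rates rest on assumed shifts, 496 completers and a simple pre-post contrast rather than the planned mixed model. They show that a shift of a quarter to a half of the 0.20 SD target (0.05/0.20 and 0.10/0.20) would be enough to mislead. They do not predict that such a shift will occur.

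The exploratory label reduces the consequence but does not remove the need for correction, because the statement concerns the primary hypothesis and how its result will be read.

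**What to change.** 1. In Study Design, restrict the low-risk-of-bias statement to the randomised feedback versus no-feedback contrast, and say that this contrast addresses the added value of feedback and not the efficacy of the game.
2. Label Hypothesis 1 an uncontrolled within-participant before-after change that cannot by itself support a causal efficacy conclusion.
3. Add this to the limitations in the Discussion.
4. Report the T0-to-T1 change, when no game is played, beside the game-period change for anxiety and for depression. Table 2 schedules both outcomes at T0 and T1, and completion is mandatory at both, so no new data are needed. The no-game interval is shorter than the game period, so this is a visible check on drift and not a correction for it.

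The article says the analysis plan will be registered before recruitment ends, so that plan and the results report can carry these changes. The cost is a few sentences and one descriptive contrast. The downside is a weaker headline claim for Hypothesis 1.
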